### Statistical plan and sample size

Inclusion is planned over approximately 3 years to estimate the cumulative incidence of Takotsubo stunning in patients hospitalised for AECOPD. The primary analysis will assess the association between a positive screening result and clinical manifestations of AHF using multivariable logistic regression. The model will adjust for relevant baseline confounders, with a significance threshold of α=0.05.

For the primary analysis, the required sample size is estimated at 150 patients, assuming a 1:10 ratio of positive to negative screening results. In previous research randomly investigating the correlation between clinical and echocardiographic signs of heart failure, clinical heart failure was present in approximately 50% of patients with echocardiographic left ventricular systolic dysfunction (LVEF <40%).^23^ Given the higher cut-off for systolic dysfunction in CATCH (LVEF <50%) and inclusion of newly detected RWMA as positive screening (ie, also in absence of reduced LVEF), together with the exclusion of patients with prior type 1 myocardial infarction or known persistent systolic dysfunction, we conservatively estimate the proportion of clinical heart failure in the positive screening group to approximately 30%. Accordingly, our sample provides 80% power to detect a difference in the incidence of clinical signs of AHF between the groups, assuming 30% in the positive screening group and 5% in the negative screening group with α=0.05.

Secondary and tertiary outcomes will be analysed using linear regression for continuous outcomes and logistic regression for dichotomous outcomes, in both unadjusted and adjusted models. A Cox proportional hazards model adjusted for baseline confounders will be applied to analyse 1-year mortality. These analyses are considered explanatory or hypothesis generating. Results will be reported as effect estimates with 95% CIs and unadjusted p values, with false discovery rate correction applied to account for multiple comparisons.^24^

Unadjusted and adjusted analyses (including covariates age and sex) will be presented as separate models. A sample size of 150 patients, with an assumed 1:10 ratio of positive to negative screening results, translates to a total number of 15 events. Given the relatively low number of expected events, all further adjustment will include only clinically meaningful covariates and will be presented as separate models.

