### Objectives and outcomes

#### Primary objectives

To determine the incidence of reversible left ventricular systolic dysfunction (as a proxy for Takotsubo stunning) in patients hospitalised for AECOPD at Sahlgrenska University Hospital (Gothenburg, Sweden).To investigate in-hospital clinical manifestations of AHF (defined as Killip class >1, table 1) in patients with signs of Takotsubo stunning versus those without, among patients hospitalised for AECOPD at Sahlgrenska University Hospital.

**Table 1 T1:** Killip classification of acute left-sided heart failure, based on clinical signs supported by chest imaging

Killip class I	No clinical/radiological signs of heart failure.
Killip class II	Clinical and radiological signs of heart failure but not pulmonary oedema (distinct bilateral rales or crackles over lungs suggesting interstitial fluid supported by interstitial fluid on chest X-ray*).
Killip class III	Clinical picture of frank pulmonary oedema supported by radiological* signs.
Killip class IV	Cardiogenic shock or hypotension (measured as systolic blood pressure lower than 90 mm Hg) and evidence of peripheral vasoconstriction (oliguria, cyanosis or sweating).

* Pulmonary ultrasound may be used to confirm Killip class.

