**Figure 1 F1:**
[figure not shown]
Screening algorithm. CATCH, Cardiac Assessment and Takotsubo-stunning among COPD-exacerbations in-Hospital; COPD, chronic obstructive pulmonary disease; RWMA, regional wall motion abnormality.

Negative=absence of RWMA and no left ventricular systolic dysfunction (LVEF ≥50%).

For patients with a positive screening result, echocardiography will be repeated after 24 (±6) hours and at 30 days (±48 hours). Within the screening-positive group, patients who demonstrate reversibility on repeat echocardiography will constitute the CATCH case group (Takotsubo stunning group), provided that no alternative cause of transient cardiac dysfunction has been identified (according to diagnostic criteria for Takotsubo^16 19^). Reversibility will be defined as normalisation or significant improvement in left ventricular systolic function, indicated by resolution of left ventricular akinesia/hypokinesia and/or improved LVEF ≥10 percentage points.

Cardiac dysfunction detected through study screening will be investigated based on clinical findings and symptoms as per clinical routine, to address alternative causes to Takotsubo stunning. For patients with ongoing or easily provoked chest pain, timely coronary angiography is mandatory to exclude coronary artery occlusion. To exclude or confirm other causes, such as myocarditis or chronic coronary syndromes, cardiac MRI or myocardial perfusion scintigraphy, respectively, may be used according to clinical routine. Hence, in cases with reversible left ventricular dysfunction, Takotsubo stunning will be validated based on clinical investigation together with diagnostic criteria for TS.^19^

If patients within the screening-positive group do not display reversibility by day 30±48 hours (or through further assessment during clinical routine follow-up within 6 months, figure 1), the RWMA and/or left ventricular systolic dysfunction will be considered persistent (ie, fulfilling exclusion criteria unknown at time of inclusion) and the patient will be excluded from analysis.

Patients who turn out negative in screening will constitute the CATCH control group.

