### Study status

Inclusion started on September 2024 and to date (April 2026), 56 patients have been enrolled (of 150 patients intended for the primary analysis). Analysis is planned after end of inclusion.

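### The primary AHF analysis is defined and powered on all screening-positive patients, but the objective and case definition concern reversible Takotsubo stunning, so the stated 80% does not carry over to that comparison

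*Protocol article*

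**What the plan says.** The exposed group for the AHF comparison is described in three places in the protocol article.

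- **Primary objectives.** The second objective compares in-hospital AHF (Killip class >1) "in patients with signs of Takotsubo stunning versus those without, among patients hospitalised for AECOPD".
- **Cardiac screening.** Among screening-positives, "patients who demonstrate reversibility on repeat echocardiography will constitute the CATCH case group (Takotsubo stunning group", provided no alternative cause of transient dysfunction is found. Dysfunction that does not reverse by day 30, or in routine follow-up within 6 months, "will be considered persistent (ie, fulfilling exclusion criteria unknown at time of inclusion) and the patient will be excluded from analysis". For the comparison group: "Patients who turn out negative in screening will constitute the CATCH control group".
- **Statistical plan and sample size.** "The primary analysis will assess the association between a positive screening result and clinical manifestations of AHF using multivariable logistic regression". The 150 patients assume a 1:10 ratio of positive to negative screening results, and the 80% power is stated "assuming 30% in the positive screening group and 5% in the negative screening group", at α=0.05.

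Study status then reports progress as "56 patients have been enrolled (of 150 patients intended for the primary analysis". No allowance is stated for positives who later leave the analysis.

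**The concern.** The three descriptions do not give the same exposed group. If every screening-positive patient is analysed, as the statistical plan says, the group includes persistent dysfunction that the Cardiac screening section removes, and the result does not speak to stunning, which is what the objective asks about. If the Cardiac screening rule is followed, the exposed group is only the reversible, otherwise unexplained part of about 14 positives, and the 80% was calculated for a larger group.

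With so few exposed patients, moving a handful in or out can change the result. A null finding in the case group could be read as 80%-powered evidence about stunning. A positive finding in all screening-positives could be credited to stunning when persistent disease contributed to it.

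**Working it through.** **Inputs from the protocol (Statistical plan and sample size).** N = 150; positive:negative = 1:10; AHF p1 = 0.30 and p2 = 0.05; α = 0.05, taken as two-sided because sidedness is not stated.

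**Input not in the protocol.** The share r of screening-positives who prove reversible without an alternative cause. I assume r = 40% to 90%.

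**Formula.** Two-proportion z-test with pooled variance under the null and no continuity correction:

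power = Φ{ [|p1 − p2| − 1.96·√(p̄(1 − p̄)(1/n1 + 1/n2))] / √(p1(1 − p1)/n1 + p2(1 − p2)/n2) }, where p̄ = (n1·p1 + n2·p2)/(n1 + n2).

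**Step 1: reproduce the plan's figure.** n1 = 150/11 = 13.64 and n2 = 136.36. Then p̄ = 0.0727, the null standard error is 0.0738 and the alternative standard error is 0.1255. Power = Φ[(0.25 − 1.96 × 0.0738)/0.1255] = Φ(0.840) = 79.96%. With whole patients (14 vs 136) it is 80.5%. The stated 80% is therefore correct for all screening-positives vs screening-negatives.

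**Step 2: check the slack.** Losing one positive (13 vs 136) gives 78.9%. At the stated rates, any loss takes power below 80%.

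**Step 3: power for reversible cases vs controls.** Here n1 = 13.64 × r, n2 stays at 136.36, and the rates stay at 30% vs 5%.

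| Assumed r | Expected cases | Pooled power |
|---|---|---|
| 90% | 12.3 | 77.6% |
| 75% | 10.2 | 73.5% |
| 60% | 8.2 | 68.4% |
| 50% | 6.8 | 64.3% |
| 40% | 5.5 | 59.5% |

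**Step 4: check the approximation.** The z-test is fragile at these counts. Exact power of Fisher's test against 136 controls is 73.7% with 14 cases, 71.9% with 13, 66.8% with 11, 61.6% with 10, 54.1% with 8 and 45.5% with 7.

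**Step 5: vary the AHF rate.** The 30% was set for all positives and need not hold in reversible cases. With 10 cases vs 136 controls, pooled power is 49% at a 20% rate, 73% at 30% and 88% at 40%.

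**Step 6: would counting 150 after exclusions restore the figure?** If 1:10 still describes screening results, the analysed ratio is r:10.

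- At r = 90%: 12.4 cases and 137.6 controls, about 78% power, with 12.4/0.9 + 137.6 = 151 enrolled.
- At r = 50%: 7.1 cases and 142.9 controls, about 66% power, with 7.1/0.5 + 142.9 = 157 enrolled.

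The shortfall is in cases, so changing how the 150 is counted barely helps.

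**The case against.** The strongest reply is that the statistical plan is consistent when read alone: it names positive vs negative screening, and the 80% fits that contrast. This is right. A reader might infer that the sample size is miscalculated or that the study is shown to be underpowered; the documents support neither.

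A second reply is that the plan should be read inside the analysis set left by the Cardiac screening rule, where the remaining positives are essentially the reversible ones and the 150 is an analysis-set target. The power loss would vanish if both the 150 and the 1:10 were meant after exclusions. But the ratio is worded as screening results, the 30% is assigned to the positive screening group, and Study status sets enrolled patients against the 150. Reversible positives with an alternative cause also remain unplaced: they are neither cases nor controls.

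A third reply concerns size. No document gives a reversible share, and because prior type 1 infarction, known RWMA and known LVEF <50% are excluded at entry, a high share cannot be ruled out. A higher AHF rate in reversible cases could offset the loss altogether. This stands: the loss is conditional, and no single power figure can replace the 80%.

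A reader might also infer that the exposed group will be picked after the data are seen. That is not established, since an analysis plan that is not shown may fix it. Such a plan would not remove the contradiction in the protocol itself.

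**Conclusion.** The point holds as an inconsistency in the definition of a primary comparison. The 80% belongs to all screening-positives vs screening-negatives. It transfers to the stunning comparison only if every positive is reversible without an alternative cause and the 30% AHF rate also applies to them, or if a higher AHF rate makes up for the lost cases.

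At 150 enrolled, with rates of 30% vs 5% and an assumed 40% to 90% reversible, power for stunning vs controls is about 59% to 78% by the pooled formula, and lower by Fisher's exact test. The range rests on an assumed share and an unchanged AHF rate, so it describes what the plan leaves open and is not an estimate of the study's actual power. The contradiction between the sections does not depend on those assumptions.

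**What to change.** Before analysis, name one exposed group for the primary AHF analysis and bring Primary objectives, Cardiac screening, and Statistical plan and sample size into line with it.

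- **If it is the reversible case group:** state that the 80% applies only to all screening-positives. Give the case group's power as a conditional range with the assumed reversible share, AHF rate and test. Say whether 150 is counted before or after exclusions.
- **If it is all screening-positives:** lift the Cardiac screening exclusion of persistent positives for this analysis. Word the conclusion as left ventricular dysfunction or RWMA at screening, and call it neither acute nor stunning, because persistent cases are included. Report reversible cases vs controls as a named separate analysis with its own conditional power.

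The cost is wording and a less favourable power figure for the stunning comparison. No added patients or procedures are required. Only a choice to count 150 after exclusions would add a few patients (about 1 to 7 at 90% to 50% reversible), and that would not by itself restore 80%.

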**Methods and analysis:**

CATCH is a prospective observational cohort study enrolling adults (≥18 years) admitted for AECOPD at Sahlgrenska University Hospital (Gothenburg, Sweden). Participants with chronic left ventricular systolic dysfunction (left ventricular ejection fraction <50%), pre-existing chronic regional wall motion abnormalities (RWMA) or prior type 1 myocardial infarction are excluded. Following informed consent, participants undergo echocardiographic screening for RWMA and/or systolic left ventricular dysfunction. Screening-positive patients have follow-up echocardiography at 24 hours (±6) and 30 days (±48 hours). Those with reversible dysfunction constitute the CATCH case group, while screening-negative participants serve as controls. Additional assessments include ECG, chest X-ray, N-terminal pro-B-type natriuretic peptide blood analysis and COPD severity. Primary outcomes include the incidence of reversible RWMA or left ventricular dysfunction (proxy for Takotsubo stunning) and in-hospital clinical signs of AHF (Killip class >1). A sample size of 150 patients is required for detecting AHF differences (α=0.05, 80% power).

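### The 80% power stated for the confounder-adjusted primary logistic regression is that of an unadjusted two-group comparison, and the adjusted model will probably have less

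*Protocol article*

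**What the plan says.** All the relevant text is in the Protocol article. Under Statistical plan and sample size, the primary analysis is defined first: "The primary analysis will assess the association between a positive screening result and clinical manifestations of AHF using multivariable logistic regression". The next sentence makes it an adjusted model: "The model will adjust for relevant baseline confounders, with a significance threshold of α=0.05".

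The sample size is then given explicitly for that analysis: "the required sample size is estimated at 150 patients, assuming a 1:10 ratio of positive to negative screening results". The planning rates are stated as "assuming 30% in the positive screening group and 5% in the negative screening group with α=0.05", and the conclusion is "Accordingly, our sample provides 80% power to detect a difference in the incidence of clinical signs of AHF between the groups". The abstract repeats the claim: "A sample size of 150 patients is required for detecting AHF differences (α=0.05, 80% power".

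The same section says that unadjusted models and models with age and sex will be shown separately, and that further adjustment will be limited because few events are expected. It does not name the formula behind 150, the sidedness, the test to be used in the logistic model (Wald or likelihood ratio), or any assumption about how the covariates relate to screening status.

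**The concern.** The power is attached to the adjusted model, yet the inputs listed are only two crude proportions, a group ratio and an alpha. A variable needs adjustment as a confounder only if it is associated with screening status, and that association costs precision. A calculation without such a term treats the association as zero, which sits badly with the stated reason for adjusting. Sex is a named covariate, and the Introduction describes Takotsubo syndrome as more than 90% female, so some association is plausible on the article's own account.

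The data are also sparse. With so few exposed patients and events, the usual large-sample agreement between the two-proportion test and the logistic tests cannot be relied on.

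If the adjusted model has less than 80% power, a non-significant primary result carries a larger chance of a missed 30% versus 5% difference than the one in five that the article implies.

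**Working it through.** **Inputs from Statistical plan and sample size.** N = 150; AHF 30% versus 5%; positive to negative 1:10, so P(positive) = 1/11; alpha 0.05. Two-sided is assumed, because the one-sided version gives 12 positives and 132 in total.

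**Step 1: reproduce the 150.** Pooled two-proportion formula, ratio k = 10:

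n₁ = [1.960·√(p̄(1−p̄)(1+1/k)) + 0.8416·√(p₁(1−p₁) + p₂(1−p₂)/k)]² / (p₁−p₂)²

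- p̄ = (0.30 + 10×0.05)/11 = 0.0727
- First term: 1.960·√(0.06744×1.1) = 0.5338
- Second term: 0.8416·√(0.21 + 0.00475) = 0.3900
- n₁ = 0.9238²/0.0625 = 13.66, so the total is 11 × 13.66 = 150.2

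Power at 150 is 79.96%. The standard sample-size formula for logistic regression on one binary covariate, with covariate R² = 0, gives the same 150.2. Unpooled variance (297) and a continuity correction (198) do not give 150. On either route that reproduces the figure, there is no allowance for adjustment.

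**Step 2: how sparse the data are.** Screening-positives: 150/11 = 13.6. Expected AHF events: 0.30×13.64 + 0.05×136.36 = 4.1 + 6.8 = 10.9. (The section's 15 events is closer to the number of positives; the stated rates imply about 11 AHF events.)

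**Step 3: exact power at N = 150, no covariates,** by binomial enumeration:

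| Group sizes | Pearson (score) | Logistic Wald | Logistic likelihood ratio |
|---|---|---|---|
| Random, P(positive) = 1/11 | 79.9% | 76.8% | 72.1% |
| Fixed 13/137 | 79.0% | 75.4% | 71.7% |
| Fixed 14/136 | 81.3% | 79.9% | 73.7% |

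The random row matches the design: a cohort screened after enrolment, with 1:10 only assumed. With 5% in both groups, the true rejection rates are 4.7% (Pearson), 3.4% (Wald) and 2.3% (likelihood ratio). Much of the shortfall in this table is therefore small-sample conservatism of the logistic tests.

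**Step 4: allowance for adjustment, closed form.** The effective sample size is N(1−R²), where R² is the share of variance in screening status explained by the covariates. R² is an assumption, since the protocol gives none.

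- R² = 0.1: effective N = 135, power 77.0%; N for 80% = 150.2/0.9, rounded up to 167
- R² = 0.2: effective N = 120, power 73.6%; N for 80% = 150.2/0.8, rounded up to 188

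With the exact logistic tests and random group sizes, effective N = 135 gives 73% (Wald) and 68% (likelihood ratio).

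**Step 5: simulated logistic regression adjusted for two covariates,** random group sizes, about 4000–5000 runs per scenario (Monte Carlo error about 0.7 points). All covariate distributions are assumptions.

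| Assumed covariate association | Wald | Likelihood ratio |
|---|---|---|
| None with screening status | 76–77% | 72–74% |
| 75% versus 55% female | 75% | 71% |
| 90% versus 55% female, or age 0.3 SD higher in positives with OR 1.5 per SD | 73% | 70–71% |
| Both of the last | 69% | 67% |
| Prognostic covariates, age shifted 0.5 SD | 69% | 65% |

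With a fixed 14/136 split and no association with screening status, the adjusted model gives 78–80% (Wald) and 75–76% (likelihood ratio).

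**The case against.** Several objections have force.

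- **The arithmetic is right.** The stated inputs return the stated N and power. A reader might infer that 150 came from a z-test, and so from the wrong formula. The article names no method, and a logistic formula with R² = 0 returns the same 150.2. What stands is only that neither route allows for adjustment.
- **Random group sizes are not the cause.** A reader might blame the unfixed number of positives, but the Pearson test still averages 79.9% with random sizes. They matter for the logistic tests, mainly Wald (79.9% at fixed 14/136, 76.8% when random).
- **Some admissible choices keep about 80%.** Fixed 14/136 with a Wald test and no confounding gives 78–80%. Exactly 15 positives gives 81.5% for the unadjusted Wald test. The large-sample Wald formula gives 84%, although with about 11 events it is a poor guide; exact enumeration at 14/136 gives 79.9%. It is therefore not supportable to say that the plan's own inputs yield a power in the high sixties. Figures that low require covariate distributions that the protocol does not contain.
- **The unadjusted result will also be reported, and the article acknowledges few events.** This is true, and it limits the harm. But the section defines the primary analysis as the adjusted model and ties the sample size to it.
- **The gap is smaller than the uncertainty in 30%, 5% and 1:10.** This is fair, and it argues against changing N. It does not justify attaching the figure to a model for which it was not derived.

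**Conclusion.** The concern holds in a limited form. The 80% at 150 patients is correct for an unadjusted comparison of 30% with 5%. The article states it for a confounder-adjusted logistic regression without any allowance for the adjustment.

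Under the plan's own rates and ratio, with the number of positives random, the unadjusted logistic model has about 77% (Wald) or 72% (likelihood ratio). Covariates associated with screening status reduce this further: roughly 65–75% in simulation, or 77% to 74% by formula at R² of 0.1 to 0.2. The chance of missing the assumed difference is then about one in four to one in three.

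The size rests on the choice of test and on assumed covariate associations, so no single replacement figure can be read from the protocol. The error lies in what the power is claimed for. It is neither a miscalculation nor a reason to call the design invalid.

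**What to change.** Keep 150 patients. In the abstract and in Statistical plan and sample size, say that the 80% applies to the unadjusted comparison of 30% with 5% at 1:10, two-sided 0.05. Add that power for the planned adjusted logistic regression is lower. Give it as a range from a short simulation of that model, with a random number of positives, age and sex included, and the covariate assumptions and the test to be reported both stated.

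The cost is two sentences and a short simulation, with no extra patients or procedures. The stated power becomes somewhat less favourable. The article reports 56 of 150 patients enrolled and analysis only after inclusion ends, so the change can still be made before the data are analysed.

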#### Tertiary objectives

The tertiary objectives include investigations within three distinct groups of AECOPD: (1) patients with evidence of Takotsubo stunning, (2) patients without evidence of Takotsubo stunning and (3) the overall cohort, including both patients with and without Takotsubo stunning. In accordance with the secondary objectives, these analyses will also be conducted within a hypothesis-generating framework.

Concordance between echocardiography, chest X-ray and NT-proBNP in displaying signs of heart failure.Prevalence of right ventricular pathology.Prevalence of diastolic dysfunction.The association between NT-proBNP and in-hospital outcome.The association between Killip classification and in-hospital outcome.

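### The regression assigned to tertiary outcomes measures association, so it does not answer the one tertiary objective that asks about concordance between echocardiography, chest X-ray and NT-proBNP

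*Protocol article*

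**What the plan says.** The first item under Tertiary objectives is "Concordance between echocardiography, chest X-ray and NT-proBNP in displaying signs of heart failure". The same section sets the populations: "The tertiary objectives include investigations within three distinct groups of AECOPD", namely patients with evidence of stunning, patients without it, and the two combined. It also sets the status: "these analyses will also be conducted within a hypothesis-generating framework".

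The method is in Statistical plan and sample size: "Secondary and tertiary outcomes will be analysed using linear regression for continuous outcomes and logistic regression for dichotomous outcomes", with and without adjustment. The only other model named there is a Cox model for 1-year mortality. The form of reporting is also fixed: "Results will be reported as effect estimates with 95% CIs and unadjusted p values, with false discovery rate correction applied to account for multiple comparisons".

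The article names no agreement measure (percent agreement, kappa, or sensitivity and specificity). It gives no NT-proBNP cut-off for a sign of heart failure. The Outcomes section lists primary and secondary outcomes only, so the analysis section's reference to tertiary outcomes can only point to the list of tertiary objectives.

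**The concern.** Concordance asks whether two tests classify the same patient the same way. Logistic regression of one test on another gives an odds ratio, and linear regression of NT-proBNP on the echocardiographic result gives a mean difference. Both describe how results move together. Neither shows systematic disagreement: one test may flag far more patients than the other and still have a large odds ratio. Adjusting for age and sex makes the estimate conditional on covariates, which has no role in whether two tests agree in one patient.

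The risk is that a large odds ratio is read as good concordance although the tests disagree in many patients. The article's own rationale (Scientific and clinical importance) is that the cardiac component may be masked and therefore diagnosed late or missed. The numbers missed and over-called are what this objective should show, and the effect estimate does not display them.

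**Working it through.** **The plan's own figure.** The plan states no figure for concordance. Its only sample-size figure is for the primary comparison: "the required sample size is estimated at 150 patients, assuming a 1:10 ratio of positive to negative screening results", "assuming 30% in the positive screening group and 5% in the negative screening group with α=0.05". With the pooled two-sided formula, 13.6 versus 136.4 patients and 30% versus 5% give 79.96% power, so the stated 80% reproduces. It has no bearing on this point, which concerns whether the method fits the objective.

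**Inputs for the illustration.** N = 150 is from the plan. The 15 echo-positive patients follow the plan's own count of 15 (a strict 1:10 split would give 150/11 = 13.6). The split of the second test within echo-positive and echo-negative patients is assumed; the documents give no positivity rates for chest X-ray or NT-proBNP.

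**Notation.** a = both positive, b = echo-positive only, c = second test positive only, d = both negative.
- Odds ratio = ad/(bc)
- Raw agreement po = (a+d)/N
- Chance agreement pe = [(a+b)(a+c) + (c+d)(b+d)]/N²
- Kappa = (po − pe)/(1 − pe)
- Positive percent agreement, echo as reference = a/(a+b); negative = d/(c+d)

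**Table A: a=8, b=7, c=9, d=126**
- Odds ratio = 8×126/(7×9) = 1008/63 = 16.0
- po = 134/150 = 0.893
- pe = (15×17 + 135×133)/22500 = 18210/22500 = 0.809
- Kappa = 0.0840/0.1907 = 0.44
- Positive agreement 8/15 = 53%; negative agreement 126/135 = 93%

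**Table B: a=14, b=1, c=63, d=72**
- Odds ratio = 14×72/(1×63) = 1008/63 = 16.0
- po = 86/150 = 0.573
- pe = (15×77 + 135×73)/22500 = 11010/22500 = 0.489
- Kappa = 0.0840/0.5107 = 0.16
- Positive agreement 14/15 = 93%; negative agreement 72/135 = 53%

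In Table A the second test misses 7 of 15 echo-positive patients and over-calls 9 of 135. In Table B it misses 1 of 15 and over-calls 63 of 135. These are opposite clinical messages with the same odds ratio.

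**What else in the output differs.** The Wald standard error of the log odds ratio is √(1/a + 1/b + 1/c + 1/d).
- A: √(1/8 + 1/7 + 1/9 + 1/126) = 0.622, so the 95% CI is exp(2.773 ± 1.96×0.622) = 4.7 to 54
- B: √(1/14 + 1 + 1/63 + 1/72) = 1.049, so the 95% CI is exp(2.773 ± 1.96×1.049) = 2.0 to 125

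The interval, the p value and the model intercept therefore differ; the odds ratio does not. Both intervals exclude 1, so both tables would be reported as a clear association.

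**Within-group check.** Under Cardiac screening, a positive screen is any regional wall motion abnormality or LVEF below 50%. The stunning group is drawn from screen-positive patients and the controls are the screen-negative ones. If the echocardiographic sign is this screening finding, it is positive in everyone in the first group and negative in everyone in the second. Neither kappa nor a regression on the echo result is then informative within those groups. Only the overall cohort, or a wider echocardiographic definition, allows an estimate.

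**The case against.** **The sentence may be a summary, and an SAP may exist.** One can read it as naming models for modelled endpoints, such as the two tertiary objectives about association, where regression fits. Concordance is not itself a patient-level continuous or dichotomous outcome, and an unseen analysis plan could add an agreement statistic. This limits the claim: the objective is unanswered by the analysis stated here, not necessarily by the study. It does not remove the point, because the article is not silent. It assigns tertiary outcomes a method and a form of reporting, and makes no exception for concordance.

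**The regression output is not identical when agreement differs.** This is right, and a reader might infer otherwise. Hold the odds ratio at (0.30/0.70)/(0.05/0.95) = 8.14 with 1 in 11 echo-positive. Second-test positivity of 30%/5% gives agreement of 0.30/11 + 0.95×10/11 = 89%, and 95%/70% gives 0.95/11 + 0.30×10/11 = 36%. At N = 150 the Wald interval moves from 2.0–32.7 (p = 0.003) to 0.7–95.6 (p = 0.10). In that extreme case the result would not look strong. These rates are also assumptions: 30%/5% is the plan's acute heart failure rate by screening result, not a chest X-ray or NT-proBNP rate. What stands is narrower. The effect estimate does not measure agreement, and a wide interval signals imprecision, not disagreement.

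**The prevalence objectives.** A reader might extend the criticism to right ventricular pathology and diastolic dysfunction, which are simple proportions. The documents do not support that. Nothing in the analysis section prevents reporting proportions, and an intercept-only logistic model returns one.

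**Kappa has weaknesses.** It depends on prevalence and is uninformative within the stunning and control groups if the echo sign is the screening result. This is accepted and shapes the fix.

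**Conclusion.** The point holds for one objective. The method assigned to tertiary outcomes estimates association, while the first tertiary objective asks for agreement. At the plan's own size, an odds ratio of 16.0 is compatible with 89% or 57% raw agreement and with kappa of 0.44 or 0.16. Those figures rest on assumed cell counts and show what is possible, not what the study will find.

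The weight is minor. The objective is tertiary and declared hypothesis generating, and no primary conclusion, sample size or data collection depends on it. It would be wrong to conclude that the tertiary analyses fail as a whole: the two association objectives suit regression, and the prevalence objectives are not obstructed by it.

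**What to change.** Exempt the concordance objective from the regression sentence and state its analysis separately:
- Define a heart-failure sign, present or absent, for each of the three tests, with the NT-proBNP cut-off fixed in advance.
- In the overall cohort, report the pairwise 2x2 tables with positive and negative percent agreement, each with a 95% confidence interval. Give kappa with its interval as a supplement.
- Within the stunning and control groups, if the echocardiographic sign is the screening finding, report only the proportions positive on chest X-ray and on NT-proBNP, and the agreement of those two with each other.

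The cost is a few sentences and no new data. Echocardiography, chest X-ray and NT-proBNP are already scheduled on the same day at inclusion for every patient (Table 2; ECG and chest X-ray; Blood samples). Study status reports 56 of 150 patients enrolled and analysis only after inclusion ends, so the change can still be made in advance. The downside is that what counts as a positive sign on each test must be agreed beforehand.
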